## Materials and methods

### Sampling design

The MATAEA project is a cross-sectional population-based survey conducted on a random sample of the general population aged from 18 to 69 years, representative of the five archipelagoes of French Polynesia. The sampling protocol is based on the previous population census dating from 2017 (1). A sample with a target size of 2,100 participants, equally divided into three age groups (18–29, 30–44 and 45–69), with a sex ratio of 1:1, was established. The sample size was determined using the following formula: *n = z² p (1-p)/d²*, where *z* is the level of confidence set at 95% (*z* = 1.96), *p* is the expected prevalence set conservatively at 50%, and *d* is the precision set at 3.7%. To represent all archipelagoes, French Polynesia was stratified into three geographical strata: Windward Islands (Society archipelago), Leeward Islands (Society archipelago), and other archipelagoes (Tuamotu, Gambier, Marquesas and Austral), which respectively include 75%, 13% and 12% of the population (Table 1). Since the population size in the Windward Islands is much higher than in the Leeward Islands and in the other archipelagoes, the sample size was amplified in the latter two strata to keep sufficient precision around prevalence estimates for the health conditions under consideration. Consequently, the same sample size of 700 subjects was chosen for the three strata, allowing a precision never exceeding +/− 3.7% around prevalence estimates within each stratum. In each stratum, for convenient reasons, the most populated islands with a health care center and an airport with regular flight rotations were selected for the study, and the number of participants to be recruited was proportional to the population size of the islands as detailed in Table 1. In each island, households were randomly selected by the *Institut de la Statistique de la Polynésie française* (ISPF, Tahiti), and in each household one resident meeting the criteria of age and sex sought for the study was recruited.

**Table 1 T1:** Geographical distribution of the 2,100 participants randomly selected for the MATAEA project.

Strata			Archipelago	Island		
Name	Population size (%)^a^	Sample size	Name	Name	Population size (%)^a^	Sample size
Windward Islands	207,333 (75%)	700	Society	Tahiti	189,517 (91%)	637
				Moorea	17,816 (9%)	63
Leeward Islands	35,393 (13%)	700	Society	Raiatea	12,249 (36%)	252
				Bora Bora	10,549 (31%)	217
				Tahaa	5,234 (15%)	105
				Huahine	6,075 (18%)	126
Others archipelagoes	33,192 (12%)	700	Tuamotu	Rangiroa	3,657 (16%)	112
				Fakarava	1,637 (7%)	49
				Hao	1,258 (5%)	35
				Makemo	1,508 (6%)	42
			Gambier	Mangareva	1,535 (7%)	49
			Marquesas	Nuku Hiva	2,951 (13%)	91
				Hiva Oa	2,243 (10%)	70
				Ua Pou	2,213 (9%)	63
			Austral	Tubuai	2,217 (9%)	63
				Rurutu	2,466 (10%)	70
				Raivavae	903 (4%)	28
				Rimatara	872 (4%)	28
Total	275,918	2,100				2,100

^a^
Data from the population census of 2017 (57).

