### Data analysis

According to the data retrieved from the participants, indicators will be defined to identify subjects suffering from, or having a history of, any pathology targeted by the study.

For continuous data, summary statistics will include the arithmetic mean with 95% confidence interval (CI) or standard deviation (SD), or median with inter quartile range. For categorical data, frequency counts, percentages, and 95% CIs will be presented. The characteristics of the subjects will be compared according to sex, age category, and geographical area using the chi-square test for the categorical variables, and using the analysis of variance (ANOVA) for the continuous variables.

Prevalence rates for each studied condition will be computed after adjusting for sampling design effects, using weights defined as the inverse probability of sampling: sampling will not be implemented with probability proportional to size but instead designed to provide a minimum stratum-specific precision of estimators, resulting in variable sampling fractions between strata. Where necessary, additional weights will also account for missing data. The main summary statistics are defined as arithmetic means along with their 95% confidence intervals (CI) adjusted for sampling design effects. Risk factors such as demographic characteristics will be evaluated using quasi-binomial regression models. Since the enrolment of participants was carried out sequentially in the different archipelagos before and after the emergence of COVID-19 (Figure 2), time and place of inclusion will be considered as potential confounders in the analyses. Analyses will be performed using appropriate statistical software such as R or STATA/SE.

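### The ±3.7% bound per stratum is the simple-random-sampling figure at 50% prevalence with no design effect, so the planned weighted estimates can exceed it near 50%

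*Protocol article*

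**What the plan says.** The Sampling design section introduces its calculation with "The sample size was determined using the following formula", which is n = z²p(1−p)/d². It states that z "is the level of confidence set at 95"% (1.96), that p "is the expected prevalence set conservatively at 50"% and that d "is the precision set at 3.7"%. It then says that "the same sample size of 700 subjects was chosen for the three strata, allowing a precision never exceeding" ±3.7% "around prevalence estimates within each stratum".

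The same section describes how people are chosen within a stratum. The target sample is divided equally over ages 18–29, 30–44 and 45–69 with a 1:1 sex ratio. Households are drawn at random on each island, and "in each household one resident meeting the criteria of age and sex sought for the study was recruited". Numbers per island are proportional to island population.

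The Data analysis section says that "Prevalence rates for each studied condition will be computed after adjusting for sampling design effects", with weights equal to the inverse of the sampling probability, confidence intervals adjusted for design effects, and further weights for missing data where needed. It explains the unequal sampling fractions only as differences between strata.

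**The concern.** The precision is worded as an upper limit for every prevalence estimate in every stratum, but it comes from a formula that assumes simple random sampling, equal weights and complete data. The design gives unequal selection probabilities inside each stratum, and the analysis section plans to weight for them. The guarantee and the intervals that will be published therefore rest on different variances.

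±3.7% is the only precision figure in the article and the sole stated basis for 700 per stratum. If it is too favourable, readers and health authorities will find some reported intervals wider than the plan told them to expect.

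**Working it through.** **Inputs from the article.** z = 1.96, p = 0.50, d = 0.037, n = 700 per stratum, equal thirds over the three age bands, one resident per household (Sampling design). Example prevalences: obesity 40.4%, hypertension 26.7%, SARS-CoV-2 infection 57.7% in adults of Tahiti (Introduction).

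**Assumed, because the article does not give them.** The design effect (deff), the population age shares, the variation of household weights, and the share of each stratum's population that is eligible.

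**1. Reproduce the plan's figure.** n = 1.96² × 0.25 / 0.037² = 701.5. Conversely, d = 1.96 × √(0.25/700) = 3.704%. The stated 700 follows from the formula with no other term, so no allowance for a design effect or for missing data is built in.

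**2. Half-width when deff is not 1.** d = 1.96 × √(deff × p(1−p)/700), and the n that keeps ±3.7% at p = 50% is deff × 701.5.

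| deff (assumed) | half-width at p = 50% | n per stratum for ±3.7% |
|---|---|---|
| 1.0 | 3.70% | 702 |
| 1.1 | 3.89% | 772 |
| 1.2 | 4.06% | 842 |
| 1.3 | 4.22% | 912 |
| 1.5 | 4.54% | 1,053 |

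**3. Age allocation alone.** With equal thirds and population shares W, the Kish weighting factor is 3 × ΣW².
- Population spread evenly over ages 18–69 (12/52, 15/52, 25/52): 3 × (144 + 225 + 625)/2704 = 1.10, so d = 3.89%.
- Assumed shares 25/31/44%: 3 × 0.3522 = 1.06, so d = 3.81%.
- Assumed younger shares 28/33/39%: 3 × 0.3394 = 1.02, so d = 3.74%.

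**4. Household weights (illustration only).** If these weights had a squared coefficient of variation of 0.05 to 0.30, the flat-age case would become 1.103 × 1.05 = 1.16 to 1.103 × 1.30 = 1.43, so d = 3.99% to 4.44%. The article gives neither household sizes nor a within-household selection rule that would fix this value.

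**5. Where the bound breaks.** The largest deff that keeps ±3.7% is (3.7/d_SRS)², where d_SRS is the simple-random-sampling half-width in percentage points.
- 57.7%: d_SRS = 3.66%, limit about 1.02.
- 40.4%: d_SRS = 3.64%, limit about 1.04.
- 26.7%: d_SRS = 3.28%, limit about 1.27.

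At deff = 1.2 the bound holds for prevalences up to about 29.5% or from about 70.5%.

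**6. Offsets.** If 65% of each stratum's population is eligible (assumed), a finite population correction gives 3.69% in the Windward Islands, 3.65% in the Leeward Islands and 3.64% in the other archipelagoes at p = 50%. It absorbs a deff of only about 1.003, 1.03 and 1.03. Stratifying by age can help more. With prevalences of 20%, 45% and 70% across the bands and flat age shares, deff is 0.93 and d = 3.58%.

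**The case against.** The strongest reply is that the plan sets p at its worst case, which leaves slack for most outcomes, and that the analysis already promises design-adjusted intervals, so published uncertainty will be right whatever the planning figure says. Recruitment ended in December 2021, so the sample size cannot change. Age allocation alone costs only about 0.03 to 0.2 percentage points, and even that needs assumed age shares. All of this stands, and it limits the point to how the precision is stated. It does not rescue a bound said to hold for every estimate: obesity, at the article's own 40.4%, breaks it at a deff of about 1.04.

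A reader might infer more than the article supports:
- **That each stratum should be treated as a cluster sample of islands, with much wider intervals.** The islands were chosen for size and access, not drawn at random, and allocation among them is proportional. That raises a coverage question, which the limitations section discloses. It does not support an added clustering variance here.
- **That taking one person per household costs a known deff of about 1.25.** The resident had to fit the age and sex sought. If that cell was set before each visit, only household members in the cell matter, and weight variation would be smaller.
- **That the national estimate breaks the promise.** Oversampling the smaller strata does cost precision for the whole territory, but the article promises ±3.7% only within strata and weights openly for that imbalance.
- **That stratum differences of 4 to 5 points will be over-read.** Even under simple random sampling, a difference between two strata at p = 50% has a half-width of 1.96 × √(2 × 0.25/700) = 5.2 points, and the reported intervals will be design-adjusted.

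**Conclusion.** The point holds in a limited form. ±3.7% is exact for p = 50%, n = 700, simple random sampling and complete data, but as a bound for every stratum-level prevalence it is too strong for the design and weighting that the article describes. Near 50%, age allocation alone puts the half-width at about ±3.7% to ±3.9% under the assumed age shares. Household and missing-data weights could widen it further, but the article does not allow that amount to be fixed. The figures of 4.0% to 4.4% in the working are illustrations, not expected values. For prevalences well away from 50%, or with steep age gradients, the bound can still hold. The consequence is a modestly optimistic planning statement; neither the weighting plan nor the planned intervals is at fault.

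**What to change.** In Sampling design, replace the upper-limit wording with a statement that ±3.7% is the half-width at 50% prevalence under simple random sampling with complete data. Add the half-width over an explicitly assumed range of design effects for n = 700: 1.1 gives ±3.9%, 1.2 gives ±4.1%, 1.3 gives ±4.2% and 1.5 gives ±4.5%. Label these values as assumptions, not as the expected precision. In Data analysis, note that sampling fractions also vary within strata, through the age allocation and the choice of one resident per household.

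The cost is a few sentences and a slightly less favourable stated precision. The sample, the weights and the analysis do not change.

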### Inclusion/exclusion criteria

The study enrolled men and women aged from 18 to 69 years at the time of enrollment, who had been residing in French Polynesia for at least six months, were affiliated to the French Polynesia social security or assimilated regimens, and were able to provide a written informed consent. Were excluded from the study minors, pregnant or parturient women, persons deprived of their liberty by a judicial or administrative decision, adults being subject to a legal protection measure or unable to express their consent, people undergoing psychiatric care, people not affiliated to the French Polynesia social security or assimilated regimens, disabled people, and the homeless.

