## Strengths and limitations

The MATAEA project is the first cross-sectional survey designed to investigate a broad range of health issues in the five archipelagoes of French Polynesia. The high number of participants and their wide geographical distribution guarantee a good representativeness of the population of French Polynesia. The large amount of data obtained for each participant from the CRF, physical measurements and biological analyses will make it possible to update the information on the prevalence of numerous NCDs and CDs known as major public health concerns in French Polynesia, and possibly identify specific indicators and/or risk factors for these diseases. The study will also provide new epidemiological information on poorly studied or unknown pathologies. Finally, the MATAEA project will generate a high amount of genetic data for a population that, so far, has been poorly represented in human genetic studies.

Nevertheless, the MATAEA project has some limitations that should be acknowledged. First, the population aged under 18 years was not included in the survey, which might have an impact on the estimate of the prevalence of certain pathologies, such as arboviral diseases and viral hepatitis. Second, participants were recruited in only 18 of the 75 inhabited islands while differences may exist between the inhabitants of distinct islands within the same archipelago. Third, there might be an underrepresentation of hard-to-reach subjects, such as heavy drinkers or socially excluded persons, which might be more prone to some pathologies. Fourth, the number of participants recruited for the study may not be sufficient to investigate rare pathologies. Fifth, the cross-sectional nature of the survey does not allow to examine the temporal relationship between exposures and diseases under study. Finally, the sampling period has been interrupted three times because of the COVID-19 pandemic and more than two years elapsed between the first and last inclusion (Figure 2). Restrictive measures implemented to prevent the spread of COVID-19 may have affected the transmission of other CDs, and also changed the study population's lifestyle habits, including diet and physical activity which are risk factors for metabolic diseases. Consequently, the time of inclusion should be considered in the analyses.

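### The sample is called representative of the five archipelagoes, but islands were chosen for convenience and the sampled islands hold only 70.7% of the remote stratum's residents

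*Protocol article*

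**What the plan says.** Sampling design in the protocol article describes a "random sample of the general population aged from 18 to 69 years, representative of the five archipelagoes of French Polynesia". It then sets out two stages.

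- Islands were not drawn at random: "for convenient reasons, the most populated islands with a health care center and an airport with regular flight rotations were selected for the study".
- Households were: "In each island, households were randomly selected by the" territory's statistics institute, with one eligible resident recruited per household.

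The same section fixes 700 participants in each of three strata. For the sample size formula it says that *p* "is the expected prevalence set conservatively at 50%, and" that *d* is 3.7%. The resulting precision is described thus: "the same sample size of 700 subjects was chosen for the three strata, allowing a precision never exceeding +/− 3.7" per cent within each stratum.

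Data analysis plans to adjust prevalence estimates "using weights defined as the inverse probability of sampling".

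Strengths and limitations says: "The high number of participants and their wide geographical distribution guarantee a good representativeness of the population of French Polynesia". A later paragraph of that section lists as a limitation that recruitment reached 18 of the 75 inhabited islands and that islands within an archipelago may differ. It does not say what share of residents was left out.

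Study objectives includes checking whether the filariasis elimination threshold has been met in every archipelago. Inclusion/exclusion criteria rules out, among others, people in psychiatric care, "disabled people, and the homeless".

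**The concern.** A random draw of households supports design-based inference only to the islands in which households could be drawn. Residents of islands passed over at the first stage had a selection probability of zero. An inverse-probability weight is undefined for them, and a larger sample would not bring them in.

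The selection rule favours larger islands with a health care center and regular flights. The Introduction itself names access to healthcare among the likely major drivers of disease burden in the Pacific islands. It is therefore an untested assumption that the omitted islands resemble the sampled ones.

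At stake is how far the remote-stratum and archipelago-level results reach. Sampling design says the Leeward and remote strata were given enlarged samples so that estimates there would be precise. A reader may take the remote figure, with its ±3.7%, as describing everyone living in Tuamotu, Gambier, Marquesas and Austral.

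**Working it through.** **1. The plan's own sample size.** With z = 1.96, p = 0.50 and d = 0.037 (Sampling design):

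n = 1.96² × 0.5 × 0.5 / 0.037² = 701.5, against the stated 700 per stratum. Conversely, n = 700 gives d = 1.96 × √(0.25/700) = 3.70%. The figure reproduces. The formula covers sampling error only and has no term for residents outside the sampled islands.

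**2. Coverage from Table 1.** The island populations in each stratum are summed and divided by the stratum total.

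- Windward: 189,517 + 17,816 = 207,333.
- Leeward: 12,249 + 10,549 + 5,234 + 6,075 = 34,107.
- Remote: 3,657 + 1,637 + 1,258 + 1,508 + 1,535 + 2,951 + 2,243 + 2,213 + 2,217 + 2,466 + 903 + 872 = 23,460.

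| Stratum | On sampled islands | Stratum total | Covered | Not covered |
|---|---|---|---|---|
| Windward | 207,333 | 207,333 | 100% | 0 |
| Leeward | 34,107 | 35,393 | 96.4% | 1,286 (3.6%) |
| Remote | 23,460 | 33,192 | 70.7% | 9,732 (29.3%) |
| All | 264,900 | 275,918 | 96.0% | 11,018 (4.0%) |

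The stratum totals add to 275,918, which matches the roughly 276,000 inhabitants given in the Introduction. The counts therefore appear to be all-age, and the uncovered share at 18–69 years may differ somewhat.

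**3. Allocation.** The remote sample follows shares of the 12 islands, not of the stratum. Rangiroa receives 112/700 = 16.0%. Its share of the 12 islands is 3,657/23,460 = 15.6%, and its share of the stratum is 3,657/33,192 = 11.0%. The 700 thus mirror the 12 islands. Table 1 gives no separate totals for the four remote archipelagoes, so whether their mix in the sample differs from that in the stratum cannot be checked.

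**4. Size of the bias in the remote stratum.** If the sampled-island prevalence is read as the stratum prevalence:

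bias = 0.293 × (difference between unsampled and sampled islands).

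The documents do not give the difference, so the values below are assumptions.

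| Assumed difference (points) | Bias (points) |
|---|---|
| 5 | 1.5 |
| 10 | 2.9 |
| 20 | 5.9 |

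The bias equals the stated 3.7 points when the difference is 3.7 / 0.293 = 12.6 points.

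**5. National estimate.** For an assumed 10-point difference in both incompletely covered strata, and strata weighted by their Table 1 totals: 0.040 × 10 = 0.4 points.

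**6. A named objective.** The Introduction lists Tahuata, Hiva Oa and Fatu Hiva in the Marquesas as not having met the filariasis threshold (antigenemia below 1%) in 2013. It also reports HBsAg of 11% in residents of Rapa born before 1992. Of these four islands, Table 1 includes only Hiva Oa. Against a 1% threshold a small gap can decide the answer. With assumed prevalences of 0.5% on sampled and 3% on unsampled islands, the remote stratum stands at 0.707 × 0.5 + 0.293 × 3 = 1.2%, while the sampled islands show 0.5%.

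**The case against.** Several points on the other side stand.

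- **Weight totals.** A reader might infer that the remote sample will be weighted up to 33,192. Data analysis names no such total. Inverse-probability weights for households drawn within 12 islands would naturally sum to the eligible residents of those islands.
- **Rescaling is no cure.** Multiplying all remote weights by a constant changes no remote prevalence. It changes only the stratum's share of the national estimate: 33,192/275,918 = 12.0% against 23,460/264,900 = 8.9%. That is about 0.3 points for an assumed 10-point difference between the remote and the other strata. If unsampled remote islands resemble sampled remote ones more than they resemble Tahiti, the 12.0% share is the better choice.
- **Disclosure.** The selection rule is stated openly, Table 1 prints the counts, and the island restriction is listed as a limitation. A charge of concealment would be wrong.
- **Scope of the claim.** The guarantee is worded for French Polynesia as a whole, where coverage is 96.0%, and all five archipelagoes were sampled.
- **Evidence of a difference.** One might infer that the omitted islands are known to differ in access to care, diet or fish exposure. No figures contrast sampled with unsampled islands on these, and Hao and Makemo, which supply the atoll contamination data, were sampled. The Introduction's disease figures do not settle it either. Tahiti, Huahine and Hiva Oa had also not met the filariasis threshold and were sampled. Rapa's 11% is close to the 10.48% found in Austral inhabitants in 1987, although dates and populations differ.
- **Exclusions.** It is tempting to say that excluding disabled people and people in psychiatric care biases non-communicable disease prevalence downward. That is plausible, but the documents define neither group by disease severity and give no numbers.

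None of this gives the remote stratum the property claimed for it. The listed limitation counts islands, not people, so it does not tell the reader that 29.3% of the stratum's residents could not be selected.

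**Conclusion.** The point holds as an overclaim confined mainly to the remote stratum. The survey is a random sample of households on 18 purposively chosen islands. Its design-based reach is complete for Windward, nearly complete for Leeward (96.4%) and 70.7% for the remote stratum. For that stratum, and for archipelago-level statements within it, neither representativeness nor a ±3.7% total error follows from the design.

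The coverage figures are exact from Table 1, subject to its counts being all-age. The bias sizes rest wholly on assumed differences; its actual size and direction are unknown. Territory-wide estimates are little affected, so a reading that the national prevalences are unsound is not supported.

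**What to change.** 1. Define the design-based target population of the remote-stratum and archipelago-level estimates as eligible adults living on the sampled islands.
2. Report coverage by stratum (100%, 96.4%, 70.7%; 96.0% overall), preferably recomputed from 18–69 census counts.
3. Limit conclusions such as the filariasis threshold to the sampled islands, and note that Tahuata, Fatu Hiva and Rapa were not sampled.
4. Give any full-stratum estimate only as a sensitivity analysis, calibrated to 18–69 census totals by archipelago, age and sex. State its assumption that unsampled islands resemble sampled ones within those cells.
5. State which weight total the remote stratum carries in the national estimate, and why. Neither the sampled-island total nor the full-stratum total is the only defensible choice.
6. Replace the guarantee with a statement of this scope, and qualify the description in Sampling design to match.
7. List the exclusion of disabled people and people in psychiatric care as a scope limitation of unknown size.

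Recruitment ended in December 2021, so island selection cannot change. The prevalence analyses are still described as future work, and no new participant data are needed. The cost is wording, census counts by age for items 2 and 4, one additional analysis if a full-stratum figure is wanted, and a narrower claim for the remote stratum.

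### Stratum-level weights leave the archipelago mix of the third stratum to the sampled islands, which hold 23,460 of its 33,192 residents; calibrating by archipelago is a cheap improvement

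*Protocol article*

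**What the plan says.** Under Sampling design, the territory is divided into three strata: Windward Islands, Leeward Islands, and all other archipelagoes together. The section states that "the same sample size of 700 subjects was chosen for the three strata". Islands were not drawn at random: "the most populated islands with a health care center and an airport with regular flight rotations were selected for the study". Within a stratum, "the number of participants to be recruited was proportional to the population size of the islands as detailed in Table 1".

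Table 1 gives the third stratum as 33,192 people and then lists 12 islands. The stratum and island columns carry the same header, but the stratum percentages are shares of the territory, while the island percentages add to 100 within the listed islands.

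The Data analysis section says prevalence will be computed "using weights defined as the inverse probability of sampling". The reason given is that the design aimed at a minimum precision per stratum, "resulting in variable sampling fractions between strata". It also plans extra weights for missing data where needed. It does not say which population total the third-stratum weights represent, and it mentions no adjustment by archipelago.

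**The concern.** The third stratum pools four archipelagoes that the Introduction describes as having different health problems: hepatitis B in the Austral, lymphatic filariasis in parts of the Marquesas, and metals in two Tuamotu atolls. A pooled prevalence for this stratum therefore depends on how much each archipelago counts.

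Residents of unsampled islands had no chance of selection, so inverse-probability weights alone cannot represent them. Scaling by a single stratum total restores the number of people but leaves the archipelago mix at that of the sampled islands. An error in that mix would be a bias in pooled estimates, and the confidence interval would not show it. At stake are the pooled third-stratum prevalences and, much less, the territory-wide ones.

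**Working it through.** **1. The plan's own figures.** Sampling design sets "level of confidence set at 95"% (z = 1.96), "expected prevalence set conservatively at 50"% and "precision set at 3.7"%. Then n = 1.96² × 0.25 / 0.037² = 701.5, against 700 stated. With n = 700 the half-width is 3.70 points. The size per stratum is reproduced.

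**2. The base of the island percentages.** Sums from Table 1:

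| Archipelago | Residents of listed islands | Quota | Share of 700 |
|---|---|---|---|
| Tuamotu | 8,060 | 238 | 34% |
| Gambier | 1,535 | 49 | 7% |
| Marquesas | 7,407 | 224 | 32% |
| Austral | 6,458 | 189 | 27% |
| Sum | 23,460 | 700 | 100% |

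- Coverage is 23,460 / 33,192 = 70.7%; the remainder is 33,192 − 23,460 = 9,732 people (29.3%).
- Rangiroa is printed as 16%: 3,657 / 23,460 = 15.6%, but 3,657 / 33,192 = 11.0%. The base is the listed islands.
- Seven times the printed percentage gives each of the 18 quotas exactly.
- For comparison, coverage is 34,107 / 35,393 = 96.4% in the Leeward stratum and 100% in the Windward stratum.

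**3. Two ways to apply the weights.** The figures per participant below are all-age residents divided by 700. They are not individual weights, which also depend on age, sex and household.

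- *Stratum total:* 33,192 / 700 = 47.4 per participant. The stratum counts as 33,192 / 275,918 = 12.0% of the territory. The archipelago mix stays near 34:7:32:27 (34.4:6.5:31.6:27.5 by residents of the listed islands).
- *Sampled islands only:* 23,460 / 700 = 33.5 per participant. The total represented is 207,333 + 34,107 + 23,460 = 264,900, so the stratum counts as 23,460 / 264,900 = 8.9%.

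**4. Size of the mix effect.** Illustration: HBsAg 10.48% in the Austral (the 1987 figure in the Introduction) and 2% elsewhere (assumption). Stratum prevalence = share × 10.48 + (1 − share) × 2.

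| Austral share | Uncovered residents this places in the Austral | Stratum prevalence |
|---|---|---|
| 27% (sampled mix) | – | 4.3% |
| 21% (assumed) | 0.21 × 33,192 − 6,458 = 512 | 3.8% |
| 35% (assumed) | 0.35 × 33,192 − 6,458 = 5,159 | 5.0% |

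The shift is −0.5 or +0.7 points. The simple sampling half-width is 1.96 × √(0.043 × 0.957 / 700) = 1.5 points. Territory-wide, the shift is 0.5 × 12.0% = 0.06 or 0.7 × 12.0% = 0.08 points.

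**5. Size of the choice of total.** The stratum's share changes by 12.03 − 8.86 = 3.17 percentage points. If the third stratum differs from the rest by an assumed 5, 10 or 20 points, the territory-wide estimate moves by about 0.16, 0.32 or 0.63 points. The simple stratified half-width at a prevalence of 50% is about 2.9 points.

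**The case against.** The strongest reply is that only a table label is missing. Much of it stands.

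- **The quotas are not wrong.** A reader might infer that they rest on a faulty base. Splitting 700 in proportion to island size depends only on relative sizes, so a base of 33,192 would give the same quotas.
- **The plan does not commit to under-counting the stratum.** A reader might infer that its weights make the remote archipelagoes 8.9% of the territory. The article never prints 23,460 and explains the weights by stratum fractions, so the stratum total is the more natural choice.
- **Weights within the stratum are not uniform.** Equal age groups, a 1:1 sex ratio and one resident per household make them vary. Only the archipelago averages are nearly equal.
- **The arithmetic bounds are too wide.** Placing none or all of the 9,732 in the Austral gives shares of 19.5% to 48.8%. Neither end can occur: the Introduction names Rapa in the Austral, and Tahuata and Fatu Hiva in the Marquesas, as inhabited islands, and none is in Table 1. The 35% case is itself demanding, since it puts 5,159 people on unsampled Austral islands although the more populated islands were selected.
- **Several aims are framed by archipelago or island**, where the pooled mix plays no part.
- **A separate analysis plan may already calibrate the weights**, and Strengths and limitations discloses that 18 of 75 inhabited islands were sampled.

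That disclosure, however, concerns differences between islands of the same archipelago. It says nothing of the weights or of the 29.3% gap. Even if every sampled island were a fair proxy for its own archipelago, the published rule would not set the archipelagoes in their census proportions.

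**Conclusion.** The point holds as a cheap improvement, not as an error that undermines the survey. Table 1 mixes two denominators under one header. The stated weighting rule, explained by strata alone, leaves the third-stratum archipelago mix to the choice of islands, and the article prints no archipelago totals against which to check it.

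The bias in a pooled third-stratum prevalence could plausibly be a third to nearly half of the sampling half-width in the hepatitis B illustration, and less if the true mix is closer to that of the sampled islands. Territory-wide it is very small from the mix, and modest even if the weights were built from the sampled islands alone.

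This rests on the assumed 2% outside the Austral, on the assumed Austral shares, and on all-age counts standing in for ages 18–69: Table 1's total of 275,918 matches the whole-population figure in the Introduction. The sample size of 700 per stratum is not in question.

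**What to change.** - **Data analysis:** calibrate (post-stratify) the inverse-probability weights to 2017 census counts of residents aged 18–69 in six areas: Windward, Leeward, Tuamotu, Gambier, Marquesas and Austral.
- **Table 1:** label the island percentages as shares of the sampled islands in the stratum, and add the census total of each archipelago.
- **Interpretation:** state that residents of unsampled islands are assumed similar to those of the sampled islands in their archipelago.

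The cost is a few lines of text and census counts from the statistics institute that drew the households. The analysis is described in the future tense, so no new data collection is needed. The downside is somewhat more variable weights in the third stratum, with Gambier resting on 49 participants. Non-coverage of the unsampled islands remains; calibration corrects the mix, not any difference between islands within an archipelago.
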